## 1. More formal description of our multiple imputation procedure

Data augmentation (DA) is the term used to refer to a Bayesian approach to impute values assuming an underlying multivariate normal model. DA first draws a random imputation of missing data given assumed values of the parameters, and then draws new parameters from a Bayesian posterior distribution based on the observed data and values imputed in the previous step. This process is repeated, and the distribution of parameters converges to a posterior distribution of the parameters that averages over the missing data. The distribution of missing data converges to a predictive distribution.

To be more precise, let the data be  $\mathbf{X} = (\mathbf{X}_o, \mathbf{X}_m)$  where  $\mathbf{X}_o$  is the observed part and  $\mathbf{X}_m$  is the missing part from a normal distribution  $\Pr(\mathbf{X}|\theta) = N(\beta, \Sigma)$ , where  $\theta$  are the unknown model parameters (conditional expectations  $\beta$  and elements of the covariance matrix  $\Sigma$ ). The goal is to replace missing values with draws from the predictive distribution of the missing data given the observed data  $\Pr(\mathbf{X}_m|\mathbf{X}_o)$ , which depends on the posterior distribution of the unknown parameters,  $\Pr(\theta|\mathbf{X}_o)$ . DA augments the observed data with the latent unobserved missing data to estimate the conditional posterior distribution  $\Pr(\theta|\mathbf{X}_o, \mathbf{X}_m)$ . For a current  $\theta^{(t)}$ , we draw  $\mathbf{X}_m^{(t+1)}$  from its conditional predictive distribution,  $\Pr(\mathbf{X}_m|\mathbf{X}_o, \theta^{(t)})$ . Next, we draw  $\theta^{(t+1)}$  from its conditional posterior distribution given the augmented data  $\Pr(\theta|\mathbf{X}_o, \mathbf{X}_m^{(t+1)})$ . This process is repeated until the specified number of imputations has been generated.

---

 It may be counterintuitive to include the dependent variables, but as von Hippel (2007) explains: “imputers sometimes worry that, by including Y in the imputation step, they are assuming something unwarranted about the X-Y relationship. This concern is misplaced. By including Y in the imputations, you are not assuming that Y has any particular relationship with X; the relationship could be positive, negative or zero, and any of these possibilities will be accounted for by the imputation model. On the other hand, if you exclude Y from the imputations, you are making an assumption. You are assuming that there is no direct relationship between X and Y.”

To obtain starting values for this procedure, an expectation-maximization (EM) algorithm is used. EM is an iterative method that predicts missing values based on the assumed values for the parameters, uses the predictions to update the parameter estimates, and repeats the process until convergence to ML parameter estimates. For the EM algorithm, we assume a non-informative uniform prior distribution for the model parameters  $(\beta, \Sigma)$ . EM convergence can be measured by the lack of change in the parameter estimates and the resulting log-likelihood. The number of iterations required for convergence is output directly from Stata.

A subset of the draws  $\mathbf{X}_m^{(t)}$  from the DA procedure are ultimately used as the imputed values. Multiple imputations begin after a specified “burn-in” period of  $b$  iterations. Because each iteration is dependent on the previous iteration, the values for each imputation are taken every  $k$  iterations, where  $k$  is the “burn-between” period. DA convergence is more difficult to measure than EM convergence but can be controlled by the burn-in and burn-between periods. The burn-in period,  $b$ , is set to obtain convergence to a stationary distribution  $\Pr(\theta, \mathbf{X}_m | \mathbf{X}_o)$  prior to recording imputed values. This is typically less than the number of iterations required by EM convergence, so a rule of thumb is to set  $b$  to a value greater than the reported iterations required for convergence of EM. The burn-between period,  $k$ , should be set large enough that the autocorrelation for all parameters has died down to 0 by lag  $k$ . We follow procedures described in the Stata Multiple Imputation manual to select values for  $b$  and  $k$ . Imputations are recorded at  $t_i = b + (i - 1)k$ , for  $i = 1 - m$ .

While more imputation draws is always better in principle, in practice there is a computational cost. Because our multiple imputation procedure is not very computationally intensive, we use  $m = 100$ , at the high end of values considered sufficient in the literature (Graham et al 2007).

## 2. Methodology after generating the imputed datasets

After imputing missing values, we re-transform each imputation of the self-control scores using the inverse-normal transformation. Then, we average the three transformed variables within each imputation to get an aggregate measure of self-control for each imputation run, 1 through  $m$ . Finally, we apply the inverse-normal transformation again to get the final self-control score for each individual in each imputation run.

Aggregating across simulation runs, pooled regression coefficients and standard errors are calculated according to Rubin’s combination rules (Rubin 1987). In particular, the estimated coefficient is the average of the coefficients estimated in each imputed dataset. With  $m$  imputations,

$$\hat{\theta} = \frac{1}{m} \sum_{i=1}^m \hat{\theta}_i.$$

The variance of the estimate is

$$\text{Var}(\hat{\theta}) = W + \left(1 + \frac{1}{m}\right) B,$$

where  $W$  is the mean within-imputation variance and  $B$  is the between-imputation variance:

$$W = \frac{1}{m} \sum_{i=1}^m W_i \text{ and } B = \frac{1}{m-1} \sum_{i=1}^m (\hat{\theta}_i - \hat{\theta})^2.$$

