#### **B. Primary right hand side variables**

- We will test the relationship between all primary outcomes and the following two key independent variables:
  - Delay ability: Expected deviation from predicted delay time in uncensored log seconds (measured in the marshmallow task at Bing preschool)
  - Self-regulatory competence: index of behavior including measure of delay ability, but also including self-control measures in 1984, 1993, and 2003

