## V. Robustness checks

- We will replicate the primary analyses using deviation from predicted delay time in uncensored seconds (rather than log seconds) to test the sensitivity of our model to the assumption of log-normality in analysis of delay time in the marshmallow task
- We will replicate the primary analyses winsorizing the key delay ability or self-regulatory competence variable at the 5th and 95th percentile
- We will replicate the primary analyses with the key independent variable of expected deviation from predicted delay time in uncensored log seconds. In these secondary tests,

- instead of estimating a model with a linear effect of deviation in delay time, we will introduce a spline with knots at the 33.3rd and 66.6th percentiles of deviation in delay time
- We will test robustness of all analyses with self-control scores in the 1984, 1993, and 2003 surveys to the imputation method used to populate missing values. Robustness checks will include:
    - Averaging of available data years (with no imputation). In the self-regulatory competence variable, we will give the available self-control indices  $\frac{3}{4}$  weight and delay ability  $\frac{1}{4}$  weight. In secondary analyses of the self-control subscales, we will average across available years
    - A multiple imputation approach for analyses with the self-regulatory competence variable (see [Section X](#) for detailed methodology)
  - In past analyses, delay time in the marshmallow task has been measured as the deviation in seconds from the condition mean delay time. As a robustness check, we will re-test the primary analysis using deviation in seconds from the condition mean delay time instead of expected deviation from predicted delay time in uncensored log seconds derived from the Tobit random effects model
  - We will test robustness of our primary findings to assumptions made during data cleaning by dropping respondents for whom we made assumptions and repeating relevant analyses

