#### **D. Self-regulatory competence: index of behavior to 2003**

- We will create a measure of self-regulatory competence as an index of behavior that includes the expected deviation from predicted delay time (in uncensored log seconds) and self-control indices in 1984, 1993, and 2003. The index will be an average of each of the four measures (transformed by the inverse normal transformation), giving equal weight to each measure. The final index will be re-transformed using the inverse normal percentile transformation to obtain a measure of persistent self-regulatory competence
  - Expected deviation from predicted delay time in uncensored log seconds
  - Self-control index in 1984
  - Self-control index in 1993
  - Self-control index in 2003
- This aggregate measure will only be calculated for subjects with at least one self-control score

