### **E. Multiple imputation of self-control scores for robustness checks**

As a robustness check, we plan to test the sensitivity of our results to the imputation method used for missing self-control scores in 1984, 1993, and 2003.

To calculate a measure of aggregate self-control, we would like to (1) normalize the self-control scores in each year (1984, 1993, and 2003) using the inverse-normal transformation, (2) average the three scores, and (3) re-normalize the final variable to get an aggregate measure of self-control as measured in 1984, 1993, and 2003. To handle missing data in this robustness check, we perform an additional step between steps 1 and 2 to impute missing self-control scores in each year. All imputation analyses are limited to the 110 subjects with a self-control score for at least one year.

As a robustness check, we use multiple imputation, a technique that incorporates random error into the imputed value to reflect uncertainty. The general idea of multiple imputation is to generate  $m > 1$  different imputed datasets, perform the analysis on each of the completed datasets (1 through  $m$ ), and pool the results of the individual analyses to get a single coefficient and standard error that simultaneously accounts for uncertainty in the coefficient estimates and uncertainty in the imputed values. Like other imputation methods, multiple imputation assumes that the data are missing at random conditional on observed variables, i.e., that the probability that the data are missing does not depend on unobserved variables.

There are different ways to draw the random error that enters into multiple imputation. We adopt one standard approach, in which it is assumed that the variables—those with missing values (the self-control measures) and those used to predict the variables with missing values—are drawn from a multivariate normal distribution. We view this approach as natural in our context because the inverse-normal transformation that we apply to many of the variables in our analysis ensures that their marginal distributions are normal.

A key modeling decision is which variables to include as predictors of the self-control measures. Best practice is to include *all* variables that play into the ultimate analyses of interest, including the dependent variables (von Hippel 2007). This is because excluding variables from the imputation that will be

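### As written, the multiple-imputation check of the competence index leaves delay ability out of the index, so it changes composition as well as imputation method

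*SAP*

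**What the plan says.** **The promise.** SAP Section V lists checks of how sensitive the self-control analyses are "to the imputation method used to populate missing values". One is "A multiple imputation approach for analyses with the self-regulatory competence variable", with Section X named as the place where the method is set out. The neighbouring check, which averages whatever years are available without imputing, states its weights: 3/4 for self-control and 1/4 for delay ability.

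**The variable.** Section III.B describes the second primary predictor as an "index of behavior including measure of delay ability, but also including self-control measures in 1984, 1993, and 2003". Section VIII.D gives the formula: "The index will be an average of each of the four measures (transformed by the inverse normal transformation), giving equal weight to each measure". The average is then transformed once more.

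**The method.** Section X.E opens with the aim "To calculate a measure of aggregate self-control". It lists three steps: normalise each year's score, average the three, re-normalise. Imputation is inserted after the first step. Section X.E.2 repeats this for each completed dataset: "we average the three transformed variables within each imputation to get an aggregate measure of self-control for each imputation run". It transforms that average into a final self-control score and goes on to pooled coefficients under Rubin's rules. Delay deviation appears in X.E only as one of the variables in the imputation model.

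**The concern.** A check of the imputation method should hold the regressor's definition fixed and vary only how missing values are filled. Followed literally, Section X.E yields a three-part score where Section VIII.D requires a four-part one. A gap between the primary and imputed coefficients would then have two possible sources, and agreement could reflect two effects that cancel.

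This matters more than usual for a robustness check. The primary index fills missing subscales with single regression predictions (Section VIII.C), and the available-year check does no imputation. Multiple imputation is therefore the only planned analysis that carries imputation uncertainty into the competence predictor, which is used in 11 of the 22 primary analyses (Section III).

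**Working it through.** The SAP states no figure on this point, so there is none to reproduce. The contradiction is one of component weights.

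| Source | Delay | 1984 | 1993 | 2003 |
|---|---|---|---|---|
| Section VIII.D, competence index | 1/4 | 1/4 | 1/4 | 1/4 |
| Section V, available-year check | 1/4 | 3/4 shared among available years | | |
| Section X.E and X.E.2, multiple imputation | 0 | 1/3 | 1/3 | 1/3 |

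**How far apart the two indices could be.** Each component has variance 1 after transformation. Let ρ be the correlation between any two yearly indices and δ the correlation of delay with each. The SAP gives neither. I assume ρ = 0.3 to 0.5 and δ = 0 to 0.2, and ignore the final rank transformation.

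- Var(4-part) = (4 + 6ρ + 6δ)/16
- Var(3-part) = (3 + 6ρ)/9
- Cov = (3 + 6ρ + 3δ)/12

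Lowest case, ρ = 0.3 and δ = 0: 0.400/√(0.3625 × 0.5333) = 0.910.
Highest case, ρ = 0.5 and δ = 0.2: 0.550/√(0.5125 × 0.6667) = 0.941.

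**What this does to a coefficient.** A correlation between indices does not show whether a conclusion would move, so I also compared standardized slopes, ignoring the gender term. Let w be the outcome's correlation with each yearly index and d its correlation with delay.

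- slope(4-part) = [(d + 3w)/4]/√Var(4-part)
- slope(3-part) = w/√Var(3-part)

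Take w = 0.15 (assumed) and d = 0.05, the SAP's prior mean for delay (Section VI.C):

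| ρ | δ | 4-part | 3-part | Shift |
|---|---|---|---|---|
| 0.3 | 0 | 0.208 | 0.205 | -0.002 |
| 0.3 | 0.2 | 0.189 | 0.205 | +0.016 |
| 0.5 | 0 | 0.189 | 0.184 | -0.005 |
| 0.5 | 0.2 | 0.175 | 0.184 | +0.009 |

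On the same grid, d = 0 gives shifts of +0.014 to +0.035, and d = 0.15 gives -0.044 to -0.021. On a wider grid (ρ = 0.2 to 0.6, δ = 0 to 0.3, d = 0 to 0.15) the extremes are about -0.04 and +0.05. The latter is a third of the SAP's 0.15 prior mean for the competence index.

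**Whether adding delay afterwards would repair it.** The three-part score has been re-normalised to variance 1. Averaging it equally with delay gives delay a nominal weight of 1/2. On the wider grid that version correlates about 0.92 to 0.98 with the Section VIII.D index. At 1/4 delay and 3/4 self-control the correlation is about 0.99 to 1.00. The combining weights therefore have to be written down.

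**The case against.** The best defence is that Section X.E describes only the self-control part. Its heading and stated aim concern missing self-control scores, and delay deviation is available for all 113 surveyed subjects (Section X.A.3), so there was nothing about it to impute. The three-score aggregate closely resembles the secondary self-control index of Section VIII.C, and the opening of the Section V item covers all analyses that use those scores. Section VIII.D is never withdrawn, and the available-year check keeps delay at 1/4, which suggests that the authors did not mean to drop it.

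Much of this stands. A reader might infer that the SAP expressly regresses on the three-part score in place of the competence index. It does not: Section X.E.2 never names the regressor. The defence still does not supply the missing step. Section V gives this check to the competence variable, Section X is the only method cited, and it contains neither a combining step nor weights.

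It is also fair to say that the size is assumed, that the shift is small at the SAP's own prior for delay, and that the available-year check already probes dependence on single imputation with the right weights. That check does not propagate imputation uncertainty.

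**Conclusion.** The point holds as a conflict between Section X.E and Sections V and VIII.D. Followed as written, the check gives delay ability a weight of 0 instead of 1/4 and so confounds the imputation method with the make-up of the index.

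A reader might go further and conclude that the check can test nothing. The documents do not support that. The two indices would probably be highly correlated, and where delay predicts outcomes as weakly as the SAP expects, the composition effect is small beside the coefficient itself. The numerical ranges rest on correlations that the SAP does not give and serve only as illustration; the conflict in weights does not depend on them.

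The primary coefficients, false discovery rate control, Wald test and Bayesian estimates are untouched. This should be corrected before the check is run, but it does not threaten the main results.

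**What to change.** In Section X.E (the three listed steps) and X.E.2, state that for the competence variable, within each imputed dataset:

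1. the three self-control indices are re-transformed;
2. they are averaged with the transformed delay deviation (log seconds) at 1/4 each;
3. that average is re-transformed;
4. the Section III regression is run, and results are pooled by Rubin's rules.

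Keep the three-score aggregate only for the secondary aggregate self-control index in Section VIII.C, and say so.

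The cost is a few sentences in the SAP and a small change in code. Delay deviation is observed for every surveyed subject and is already in the imputation model, so no imputation needs to be redone.
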